## Abstract

Poor treatment adherence and lack of self-care behaviors are significant contributors to hospital readmissions of people with heart failure (HF). A transitional program with non-invasive telemonitoring may help sustain patients and their caregivers to timely recognize signs and symptoms of exacerbation.

We will conduct a Randomized Clinical Trial (RCT) to evaluate the feasibility and acceptability of a 6-month supportive intervention for patients discharged home after cardiac decompensation. Forty-five people aged 65 years and over will be randomized to either receive a supportive intervention in addition to standard care, which combines nurse-led telephone coaching and a home-based self-monitoring vital signs program, or standard care alone. Four aspects of the feasibility will be assessed using a mixed-methods approach: process outcomes (e.g., recruitment rate), resources required (e.g., adherence to the intervention), management data (e.g., completeness of data collection), and scientific value (e.g. 90- and 180-day all-cause and HF-related readmissions, self-care capacity, quality of life, psychological well-being, mortality, etc.). Participants will be interviewed to explore preferences and satisfaction with the intervention. The study is expected to provide valuable insight into the design of a definitive RCT.

Specifications table

**Table utbl0001:** 

Subject area:	Medicine and Dentistry
More specific subject area:	*Geriatric care*
Name of your protocol:	INTERCOACH
Reagents/tools:	*Mini-COG* *Edmonton Symptom Assessment System (ESAS)* *Cumulative Illness Rating Scale (CIRS)* *European Health Literacy Survey* *SF-12 Questionnaire* *Self-Care Of Heart Failure (SCHF v. 7.2)* *Heart Failure Somatic Perception Scale v.3 (HFSPS)* *Self-Efficacy Scale* *Geriatric Depression Scale short version* *Hamilton Anxiety Scale*
Experimental design:	*A prospective, open label randomized controlled feasibility study will be conducted, with a 1:2 ratio between intervention and control groups. Participants assigned to the intervention group will receive the following educational program in addition to standard care: 1) an in-person educational intervention before discharge, following the recommendations of the European Society of Cardiology; 2) a nurse-led telephone coaching service (once a week for the initial month, followed by sessions every two weeks); 3) a daily home-based self-telemonitoring system for weight, blood pressure, heart rate, and oxygen saturation. Vital signs will be transmitted to a platform and remotely monitored by a nurse. A structured intervention protocol will be activated based on the patient's clinical conditions.*
Trial registration:	*The study protocol has been registered in the Clinicaltrials.gov:**NCT06285565*
Ethics:	*The study protocol was submitted and approved by the Ethics Committee of Maggiore della Carità Hospital of Novara in December 2023 (*CE390/2023). *The study will adhere to the Ethical Principles of the Declaration of Helsinki, as well as the European Union Standards of Good Clinical Practice* *The data from the feasibility study will be combined with those from the definitive study if it validates the suggested intervention and no substantial corrections will be required.*
Value of the Protocol:	(1) *This protocol is important to inform the design of a definitive RCT, aimed to assess the effectiveness of a remote nurse-led coaching intervention with a home telemonitoring program.* (2) *Given the complexity of the supportive intervention, it is crucial to involve patients in the research process and to collect their preferences regarding the intervention.* (3) *3) This feasibility study is important to define a successful care plan that guarantees follow-up for patients with heart failure*.

## Background

The protocol aims to develop and evaluate a complex healthcare intervention intended to enhance the care of patients discharged home following a cardiac decompensation. Transitioning from hospital to home poses significant challenges for older adults with chronic diseases, making a supportive educational intervention crucial to facilitate this process and prevent complications [[1], [2], [3]].

Generally, transitional care programs offer time-limited services and person-centered interventions to ensure continuity of care and avoid adverse events [4]. Over the past two decades, several evidence-based models have been developed [1,5]. These models include various interventions such as home visits, multidisciplinary teams, patient and caregiver self-care education, and medication reconciliation [6]. Although beneficial, these standard in-person interventions are expensive and hardly sustainable given the progressive aging of the population and the increasing incidence of chronic diseases [7,8]. Information and communication technologies enable innovative approaches to deliver care remotely, potentially reducing costs and increasing the scalability and accessibility of these interventions.

The proposed intervention is designed to tele-monitor and support the patient's self-care capacity from a distance. Given its complexity, which arises from the involvement of various stakeholders, the transition between diverse settings, and the presence of multifaceted program elements, conducting a feasibility study becomes a critical step in designing a definitive trial. Testing in advanced the intervention enables investigators to explore uncertainties and refine implementation, ultimately enhancing its effectiveness [9].

## Description of protocol

Heart failure represents a significant global health challenge, with an increasing prevalence of 0.6 % annually [10]. Home management of the disease can be daunting, especially following a hospitalization, when patients may encounter difficulties in adjusting their lifestyle to comply with the recommendations provided [11,12]. Indeed, poor treatment adherence and lack of self-care behaviors are important factors contributing to hospital readmissions [13,14].

A telephone-based supportive intervention led by nurses has the potential to enhance the self-care capacity of patients and their caregivers, thereby promoting the maintenance of healthy lifestyles. Similarly, non-invasive home telemonitoring could serve as a beneficial strategy for preventing acute decompensation by allowing healthcare professionals to remotely monitor individuals' vital signs and detect early signs of exacerbation.

Nevertheless, the effectiveness of this approach remains inconclusive even due to heterogeneity across studies, including differences in patient acuity, the level of educational support provided, follow-up durations, and the technology utilized. [[15], [16], [17], [18], [19]].

### Aim of the study

The primary aim of the study is to investigate the feasibility and acceptability of a home telemonitoring program combined with telephone-delivered nurse-led coaching intervention.

The secondary aim is to explore the feasibility of a randomized controlled study to assess the effectiveness of the supportive intervention.

## Methods

### Study design and randomization

A parallel, open label randomized controlled feasibility study will be carried out utilizing a mixed method approach. The protocol complies with the criteria reported by SPIRIT 2013 statement [20]. We will generate a list of randomizations stratified by wards and gender, with a 1:2 ratio between intervention and control groups, using web-based software.

### Population and enrollment

Patients will be enrolled in three medical wards of a large University Italian hospital at the time of discharge and will be followed in the domiciliary setting. Sequentially numbered sealed, opaque envelopes will be used to conceal the allocation.

### Inclusion and exclusion criteria

All patients aged 65 and over, hospitalized for cardiac decompensation, regardless of ejection fraction value (preserved or decreased), and expected to be discharged home will be considered eligible.

Individuals who lack the cognitive and/or physical capabilities (POSITIVE Mini-COG)) [21] for self-monitoring of vital signs, and without a caregiver available to assist them, will be excluded. In addition, individuals who are receiving ongoing medical care from other services will also be excluded.

### Sample size

As this is a feasibility study, it is not required to calculate the sample size [22]. Instead, the sample must be representative of the reference population [22]. Accordingly, it is planned to recruit 45 patients (15 will be allocated to the intervention arm and 30 to the control arm).

### Intervention group

A supportive program will be provided in addition to standard care, consisting of 1) a pre-discharge educational meeting, 2) telephone nurse-led coaching sessions and 3) home telemonitoring of vital signs.(1)*Pre-discharge educational meeting.* After the patient is deemed stable by the clinicians, an in-hospital educational intervention will be provided by a trained nurse not involved in the clinical pathway. Family members will be invited to participate but attendance will not be mandatory. Key topics of self-care management recognized by the European Society of Cardiology will be discussed, including the importance of physical activity, rest and sleep quality, fluid restriction, a healthy diet, medication adherence, the advantages of immunization, smoking cessation, psychological issues, need for formal and informal support [23].During the meeting, the nurse will use the Transtheoretical Model of Prochaska & DiClemente [24] to identify the individual's priority goals and motivation for change, thus initiating the coaching session. The model recognizes five stages of change:-pre-contemplation: not yet recognizing the existence of problematic behavior that requires change.-contemplation: recognizing the presence of a problem but not yet being prepared, certain, or confident about the desire or ability to enact a change.-determination: preparing to change behavior.-action: taking action to change behavior.-maintenance: maintaining the changed behavior.(2)*Telephone nurse-led coaching sessions.* In this phase, patients will be encouraged to focus on their values and progress towards their goals. The intervention will be tailored based on the stage for change and personal difficulties reported by the individual during the initial meeting (e.g. if the patient is in the pre-contemplation phase, the nurse will adopt an informative approach). The scheduled sessions will occur weekly during the first month and then transition to twice a month thereafter. If the person is unavailable, a second attempt will be made the following day at the same time.(3)*Home telemonitoring of vital signs*. Patients will receive education on measuring weight, blood pressure, heart rate, and oxygen saturation at rest every morning before breakfast. All participants will be provided with a telemonitoring system connected to a smartphone, which acts as a gateway and transmits data to a web platform via Bluetooth.

The system will be equipped with alarms to signal deviations in vital signs from predefined ranges. Upon notification, the nurse will contact the patient within 72 h (excluding Saturdays, Sundays, and holidays) to assess the presence of symptoms and/or signs of congestion. Patients will be asked the following questions: “Are you short of breath?” Describe the sensation on a 0–10 scale, where 0 means no shortness of breath and 10 severe shortness of breath. By the Edmonton Symptom Assessment System (ESAS) scale [25], scores ≤4 will be considered mild; 5–7 moderate; ≥ 8 severe. “By applying pressure with your finger to the area near the ankle, do you observe an indentation? Have you had trouble tying your shoes in the last few days?” The questions will be assessed on dichotomous (yes/no) scales. Depending on the conditions of the person, a multidisciplinary protocol will be implemented (Table 1).

**Table 1 tbl0001:** Intervention protocol in the event the nurse identifies an alteration in vital signs through remote telemonitoring.

Signs and symptoms alterations	Multidisciplinary interventions
*Systolic blood pressure* <90 or >150 mm/Hg and/or *Heart rate* <60 or >100 bpm and/or *± 2**kg in the last three days.* *and/or* *≤92 % oxygen saturation* **Without or mild symptoms** (ESAS *Score Scale ≤4)*	Self-management interventions will be reinforced as needed, with re-evaluation in the days following. If alterations persist for three consecutive days, referral to the patient's physician will be recommended
*Systolic blood pressure* <90 or >150 mm/Hg and/or *Heart rate* <60 or >100 bpm and/or *± 2**kg in the last three days.* *and/or* *≤92 % oxygen saturation* **With moderate symptoms** (ESAS Score Scale 5–7)	The nurse will request an assessment or consultation from the physician of the hospital ward where the patient was admitted
*Systolic blood pressure* *<90 or >150**mm/Hg* *and/or* *Heart rate* *<60 or >100 bpm* *and/or* *± 2**kg in the last three days* *and/or* *≤92 % oxygen saturation* **With severe symptoms** (ESAS Score Scale ≥ 8)	Referral to the emergency service

Before hospital discharge, the physician will specify a dry weight to be maintained and the dosage of a loop-type diuretic (i.e., torsemide or furosemide) for clinical stability. In the event of a weight gain exceeding 2 kg within three days (with no other symptoms), consistent with previous days and under identical conditions, the diuretic dosage will be doubled for three days [23].

The patients can contact the nurse by telephone from Monday through Friday from 8:30 a.m. to 5:30 p.m. or request a home visit. This service does not replace the emergency services.

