The following outcomes will be measured:-*Recruitment rate:* the proportion of patients who agreed to participate relative to those who fulfilled the inclusion criteria.-*Retention rate*: the proportion of patients who complete the study relative to those who consent to participate.--*Adherence to the coaching intervention:* the number of coaching phone calls scheduled relative to those actualized.-*Adherence to telemonitoring program:* the proportion of days during which vital signs were measured and sent by the system relative to the total duration of the intervention.-*Weekly time dedicated to coaching intervention by the nurse* (in hours).-*Completeness of data collection:* the number of returned questionnaires.-*Number of weekly calls made by patients to the nurse.*-*Quality of life*: Quality of life is a value that integrates objective (physical health, personal circumstances, social relationships, social and economic influences) and subjective indicators (such as how the individual responds to objective conditions), related to various dimensions of life and personal values [28]. This outcome will be assessed using the Italian version of the SF-12 scale [29]. This is a multidimensional scale consisting of 12 questions related to physical functioning, limitations due to physical health or emotional factors, energy and fatigue, emotional well-being, social activities, pain, and general health perception. The scale collects self-report data using a Likert scale. The score for each subscale will be standardized on a 0–100 scale, where higher values indicate better quality of life.-*Self-care capacity*: The self-care capacity of the patient encompasses three dimensions: self-care maintenance, symptom perception, and self-care management [30]. Self-care maintenance reflects the active commitment and responsibility for one's own care, as well as the behaviors adopted to maintain physical and emotional stability (e.g., adherence to therapy). On the other hand, symptom perception refers to the ability to respond to signs and symptoms of disease exacerbation when they occur, such as by searching for help (self-care management) [30]. The self-care capacity will be evaluated using the Italian version of the Self-Care of Heart Failure Index (SCHF v. 7.2) [31]. The tool consists of three different scales: self-care maintenance (10 items), symptom perception (11 items), and self-care management (8 items) producing a standardized score of 0–100, where higher values refer to the greater self-care capacity. A score ≥70 indicates adequate self-care capacity.-*Self-Efficacy Scale:* Self-efficacy perception refers to the individual's belief in their ability to achieve certain goals because of their actions, regardless of the challenges and difficulties they may face [32]. Self-efficacy is a mediator of self-care capacity [32]. A scale consisting of 10 items using a 5-response Likert scale will be utilized [33].-*Heart Failure Somatic Perception Scale v.3* (HFSPS) [34]. HF is a complex clinical syndrome characterized by several signs and symptoms, including shortness of breath, fatigue, and peripheral fluid accumulation [23]. To measure this outcome, we will employ a scale comprising four factors, which evaluate the presence and impact of 18 typical signs and symptoms of HF experienced by the patient in the preceding week. Each item has 6 response options ranging from 0 (I do not have this symptom) to 5 (extremely severe), with a range from 0 to 90, where high scores lead back to a greater impact of symptoms on the patient.-*Geriatric Depression Scale short version* (GDS) [35] for detecting depressive symptoms of the elderly. It consists of 15 questions involving a dichotomous response (yes/no). Ten questions are indicative of depression for positive responses, while the remaining five (items 1, 5, 7, 11, 13) for negative responses. Scores 0–4 are considered normal, depending on age and education; scores between 3 ± 2 are associated with the absence of depressive symptoms, 7 ± 3 mild depression, and 12 ± 2 depression.-*Hamilton Anxiety Scale* [36]: for the assessment of anxiety symptoms (psychological and somatic). The scale consists of 14 items, rated on a 4-point Likert scale (0=not present; 4= severe), with a range of total score from 0 to 56, where values ≤ 17 indicate mild anxiety, 18–24 moderate anxiety and ≥ 25 severe anxiety.-*Hospital readmissions at 90- and 180- days* after hospitalization for all causes and HF-related, Emergency Departments visits, outpatient visits, General Practitioner visits, and mortality.

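### After a gain above 2 kg in three days, the diuretic is doubled without symptoms, but mild breathlessness (ESAS 1–4) brings no diuretic step and no prompt medical review

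*Protocol article*

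**What the plan says.** All the rules are in the Intervention group section of the Protocol article, including Table 1.

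- **The call.** After an alarm the nurse has 72 hours to reach the patient ("excluding Saturdays, Sundays, and holidays) to assess the presence of symptoms and/or signs of congestion"). Breathlessness is scored from 0 to 10, and "scores ≤4 will be considered mild"; 5–7 is moderate and 8 or more is severe. Two yes/no questions follow: "do you observe an indentation? Have you had trouble tying your shoes in the last few days".
- **Table 1.** The three rows share the same vital-sign limits, including a change of 2 kg over three days, and differ only in the ESAS band. Row 1 is labelled "Without or mild symptoms" (ESAS 4 or less). Its action is "Self-management interventions will be reinforced as needed, with re-evaluation in the days following. If alterations persist for three consecutive days", after which referral to the patient's physician is recommended. Row 2 (5–7) brings in the physician of the discharging ward. Row 3 (8 or more) goes to the emergency service.
- **The diuretic rule.** A separate sentence below the table covers a gain of more than 2 kg and sets this condition and action: "within three days (with no other symptoms), consistent with previous days and under identical conditions, the diuretic dosage will be doubled for three days". Before discharge the physician specifies a dry weight and a loop-diuretic dose.

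**The concern.** A response rule should not weaken as the patient gets worse. Here the only written treatment step below ESAS 5 is tied to the absence of other symptoms, and the row that takes the mildly breathless patient offers neither that step nor an early medical opinion. Weight gain with beginning breathlessness is the kind of early exacerbation that telemonitoring is meant to detect, according to the Description of protocol section.

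The call is also meant to look for signs of congestion, yet the answers to the two congestion questions do not feed into the table.

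At stake are the safety of intervention patients and the quality of the intervention being tested, possibly including readmissions. The Specifications table foresees combining these data with the definitive trial if no substantial corrections are needed, which is a reason to settle the rule before recruitment.

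**Working it through.** The plan states no figure to reproduce. The check applies the written rules to one event, a gain above 2 kg in three days, and varies what the nurse hears at the call.

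| Heard at the call | Table 1 row | Diuretic rule, read literally | Medical involvement |
|---|---|---|---|
| ESAS 0, both congestion answers no | 1 | Doubled for three days | Patient's physician if altered three days running |
| ESAS 0, a congestion answer yes | 1 | Doubled, or not if the sign counts as a symptom | As above |
| ESAS 1–4, any congestion answer | 1 | Not doubled | As above |
| ESAS 5–7, any congestion answer | 2 | Not doubled by rule | Ward physician |
| ESAS 8–10, any congestion answer | 3 | Not doubled by rule | Emergency service |

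**Breathlessness.** Row 1 holds five scores (0, 1, 2, 3, 4). The diuretic rule applies to one of them, so 5 − 1 = 4 scores have row 1 alone. These are scale points, not patients. Row 1 applies to the symptom-free patient as well, who gets everything in it plus the doubled dose.

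**Congestion answers.** Lines 1 and 2 of the table share a row, and the answers make no difference in lines 3 to 5. Their only possible effect is through the condition of no other symptoms, where a yes would remove the doubling and add nothing.

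**Timing of the referral in row 1** (no public holidays assumed):

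- Latest contact: 72 h = 3 days if no weekend hours fall in the window, and 3 + 2 = 5 days if a whole weekend does. Contact therefore falls on day 0 to 5 after the alarm.
- If persistence counts from the first altered reading, referral falls on max(3, contact day) = day 3 to day 5.
- If persistence counts from the call, referral falls on contact day + 3 = day 3 to day 8.
- Measured from the call, the wait is 0 to 3 days. If doubling starts at the call (an assumption), then at the upper end the symptom-free patient has finished the three-day course when referral is first recommended for the mildly breathless one.

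Day 8 combines the latest contact with the less favourable way of counting. Readings are taken every morning and transmitted, so counting from the first altered reading is workable, and day 3 to 5 is then the range. The physician's own waiting time is not given.

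**The case against.** **The condition may mean isolated weight gain.** The ESAS bands have no separate class for no symptoms, since 0 falls within mild, and row 1 pools the two. The parenthesis could mean that nothing moves the patient to a higher row. On that reading ESAS 1–4 would also be doubled and the reversal disappears. The reading is possible, so the wording is at least ambiguous. Against it, the label of row 1 names no symptoms and mild symptoms as two states, and a nurse has to apply the words as printed. The congestion answers would still lead to no row.

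**Withholding automatic doubling from a symptomatic patient may be deliberate caution.** This is a sound clinical reason, and the guideline cited for the rule is not available here. It explains the missing diuretic step but not the missing review: where a protocol dose change is thought unsafe, a physician should decide, and row 1 brings one in only after persistence.

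**The article is condensed, and the full call procedure may say more.** That would answer a charge of omission. The article, however, prints both the table and the diuretic rule, and the mismatch lies between them.

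**There are other safeguards.** Patients may telephone the nurse on weekdays or ask for a home visit, and a rise to ESAS 5 or more at re-evaluation brings help sooner. Both stand and limit the consequence.

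**Stronger readings that the text does not support.** A reader might infer that the mildly breathless patient gets nothing but reinforcement; row 1 also sets re-evaluation and the conditional referral. A reader might infer that the feasibility results are distorted. Coaching adherence ("the number of coaching phone calls scheduled relative to those actualized") and telemonitoring adherence ("the proportion of days during which vital signs were measured and sent by the system") do not depend on what follows an alarm. Nor do the documents show that anyone would be harmed, or how often.

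**Conclusion.** The point holds as a flaw in the stated intervention rules. Read literally, a gain above 2 kg with ESAS 1–4 meets a weaker response than the same gain with ESAS 0: no diuretic step and no prompt medical review. The two congestion answers have no row of their own and can at most take the doubling away.

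The conclusion rests on reading the absence of other symptoms as excluding mild breathlessness, which the row 1 label supports but the text does not settle. The referral timing also depends on when doubling starts and how persistence is counted, neither of which is stated.

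The exposure is at most the 15 patients planned for the intervention arm (Sample size section). The rule should be corrected because it governs drug treatment in older patients recently discharged after decompensation. It does not threaten the main feasibility estimates.

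**What to change.** 1. Move the diuretic rule into row 1 and define its condition: gain above 2 kg in three days, ESAS 0, neither congestion answer positive, and no other vital sign outside its limits.
2. Add to row 2 a gain above 2 kg in three days with ESAS 1–4, or with a new or worse congestion answer. The ward physician is then consulted and decides on the diuretic.
3. Ask the two congestion questions once before discharge, so that a later yes can be judged as new. A yes/no answer cannot show worsening, so the nurse needs a short prompt for that.
4. State where two remaining cases go at ESAS 0: a positive answer unchanged since discharge, and a gain together with another altered vital sign. Row 2 is the cautious choice; otherwise these patients lose doubling with nothing in its place.

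Simply widening doubling to everyone with ESAS 4 or less is not advised. Row 1 includes systolic pressure below 90, so a patient with low pressure could have the dose doubled without review.

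The cost is edits to Table 1 and the diuretic sentence, two questions asked once in 15 patients, and some extra ward-physician consultations. Their number cannot be estimated because alarm frequency is unknown. No extra staff are needed.

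### The rule that doubles the loop diuretic after a weight gain does not, as worded, exclude a patient whose systolic pressure is below 90 mmHg

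*Protocol article*

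**What the plan says.** All of this is in the protocol article, section Intervention group.

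- **Doubling rule (paragraph after Table 1).** It opens "In the event of a weight gain exceeding" 2 kg within three days and continues "with no other symptoms), consistent with previous days and under identical conditions, the diuretic dosage will be doubled for three days". Before discharge the physician sets a dry weight and a loop-diuretic dose. No blood pressure floor or hold criterion is mentioned.
- **Table 1, left column.** Headed "Signs and symptoms alterations". Every row lists the same alarms, joined by and/or: systolic pressure <90 or >150, heart rate <60 or >100, a 2 kg change either way in three days, saturation ≤92 %. The rows differ only in the symptom grade, taken from the ESAS score.
- **Table 1, first row.** For alarms "Without or mild symptoms" (ESAS ≤4), the action is "Self-management interventions will be reinforced as needed, with re-evaluation in the days following". A recommendation to see the patient's physician follows "If alterations persist for three consecutive days".
- **Table 1, second row.** For moderate symptoms, "The nurse will request an assessment or consultation from the physician of the hospital ward where the patient was admitted".
- **Nurse call after an alarm.** Due within 72 h ("excluding Saturdays, Sundays, and holidays) to assess the presence of symptoms and/or signs of congestion"). The scripted questions cover breathlessness, ankle indentation and difficulty tying shoes.

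**The concern.** The rule fixes a trigger, an exclusion, a dose change and a duration, so it is an operational instruction. Its exclusion is framed in terms of symptoms, and Table 1 treats low pressure as something a symptom-free patient can have. A patient can therefore meet every written condition for doubling with a systolic pressure that the protocol itself flags as abnormal.

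At stake is the safety of patients aged 65 and over who have recently decompensated and are managed at a distance. Doubling a loop diuretic when systolic pressure is already below 90 mmHg may lower it further. The information needed to prevent this is already collected: patients measure blood pressure in the same morning session as weight.

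**Working it through.** The plan states no derived figure on this point, so the check sets the written conditions against a hypothetical patient.

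**Test patient (assumed for illustration):** weight +2.5 kg over three days, confirmed on consistent readings under the same conditions; systolic pressure 85 mmHg; heart rate and saturation within limits; no breathlessness, no ankle indentation, no trouble tying shoes.

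1. *Weight trigger.* 2.5 kg > 2 kg within three days: met.
2. *Consistency and identical conditions.* Met by construction.
3. *No other symptoms.* The scripted questions are all answered no, so this is met if symptoms means what Table 1 grades. Those questions concern congestion; none asks about dizziness or other effects of low pressure.
4. *Condition on pressure, heart rate or saturation in the doubling sentence.* None is written.
5. *Result of the doubling rule.* Dose doubled for three days.

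**The same patient in Table 1:** 85 < 90 gives a pressure alarm, the gain gives a weight alarm, and the and/or wording lets both apply together. With no symptoms the patient falls in the first row. That row names no drug change, so it neither authorises nor blocks the doubling. The second-row route to the ward physician needs an ESAS score of 5–7, so it is not triggered.

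**Day count,** assuming the gain and the low pressure are first seen on day 1 and doubling starts that day:

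- doubled dose: days 1, 2, 3;
- first-row recommendation to see the physician: after alterations on days 1, 2 and 3, so day 3 at the earliest.

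Under that assumption, the physician recommendation falls due no earlier than the last day of the doubled course. If doubling starts later than day 1, the recommendation falls earlier within the course, but the text still requires no physician contact before the first doubled dose.

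**Search for a safeguard elsewhere in the article:** the pre-discharge physician input covers dry weight and dose only; the weekday telephone line and home visits are at the patient's request; no sentence says how the doubling rule and the first row relate to each other. None supplies a pressure check before doubling.

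**The case against.** **An isolated gain was meant.** The word *other* follows directly on a measured weight gain, so the sentence seems to count the gain itself as a symptom, and the Table 1 column head groups signs with symptoms. On that reading a low pressure is already excluded. This is plausible and may well be the intention. It does not settle the matter, because the first row of the same table expressly allows a pressure alarm in a patient without symptoms. A dosing instruction with two tenable readings, one of which doubles a diuretic at systolic <90, needs a clearer sentence.

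**The article is condensed.** The sentence cites a clinical guideline, does not say who decides on the doubling, and may be completed by the full protocol or by an individual discharge instruction. A safeguard there is possible, and the article does not show that clinicians would double the dose regardless. What stands is narrower: the rule as published gives its own exclusion, and that exclusion is too loose.

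**A nurse sees the readings.** Vital signs are monitored remotely by a nurse, an alarm prompts a call, and the first row includes re-evaluation in the following days. This lowers the practical risk, since a nurse who calls before any dose change can see the pressure. It does not tell the nurse what to do with it.

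**Stronger readings that the documents do not support.** A reader might infer that, because the call window skips weekends and holidays, a doubled course could be over before anyone calls. That requires the patient to start doubling before the call, a sequence the article nowhere states. A reader might also want doubling withheld for every concurrent alarm. No harm from doubling is shown for systolic >150, an abnormal heart rate or saturation ≤92 %, and a gain with high pressure or low saturation could be fluid overload, where waiting for a physician may delay decongestion. Finally, the first row and the doubling rule need not contradict each other; they can be applied together.

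**Conclusion.** The point holds as a matter of wording. The doubling rule does not exclude a patient with a qualifying gain, no symptoms and systolic pressure <90, and nothing else in the article requires a physician to be contacted first in that case.

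It is a minor-to-moderate safety clarification. It concerns only the 15 patients planned for the intervention arm. The documents give no frequency for the combination, so no number of affected patients can be stated. No endpoint or analysis changes.

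The conclusion rests on two assumptions: that *symptoms* in the doubling sentence carries the meaning it has in Table 1, and that no pressure limit is set in a document not shown. If either fails, the published sentence would still benefit from saying so.

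**What to change.** Add one condition to the doubling sentence, for example: *and that morning's systolic pressure is not below 90 mmHg; if it is, the nurse consults the ward physician before any dose change.* The consultation can use the route already written in the second row of Table 1. Add that the doubling rule otherwise applies alongside the first row.

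The cost is one edited sentence and a short briefing for the nurses. No measurement is added, because pressure is already taken with the weight each morning. The downside is an occasional extra physician call. The other alarms should stay as they are.
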